### Eligibility criteria/subjects

Participants are identified as potential subjects for this study if they are over 50 years of age, under the care of one of the participating surgeons, and elect to have RTSA for rotator cuff tear arthropathy, massive irreparable rotator cuff tear, or primary osteoarthritis. Subjects are excluded from study participation for the following reasons: history of prior ipsilateral open shoulder surgery, non-reverse total shoulder arthroplasty, RTSA for fracture or revision arthroplasty, RTSA with a tendon transfer, discharge to a skilled nursing facility, in-patient rehabilitation placement, or use of home health therapy prior to progressing in recovery, unwilling to make a good faith effort to adhere to their randomly prescribed rehabilitation scheme, unable to speak, read, or write the English language, have cognitive deficits limiting ability to follow direction, unable or unwilling to be randomised due to financial or personal constraints, or have inability to attend physical therapy (i.e. transportation or financial limitations). Subjects who meet the inclusion criteria are identified at clinical appointments with participating surgeons, and clinical research assistants discuss the study process and review the voluntary informed consent process. At this appointment the following variables are obtained as pre-operative baseline values: American Shoulder and Elbow Surgery (ASES) score, Numeric Pain Rating Scale (NPRS) level, Single Assessment Numeric Evaluation (SANE) score, active range of motion (AROM), passive range of motion (PROM), and Patient-Reported Outcomes Measurement Information System (PROMIS) score. Upon voluntary consent to participate, clinical research assistants employ computer based Research Electronic Database Capture (REDCap) (Nashville, TN) [36] to perform the allocation sequencing of subjects to either the PT or HT group. The randomization schedule is a randomized block design stratified by site using a 1:1 treatment allocation in blocks of size 8.. Patients are encouraged to remain within the group to which they are randomly assigned for the duration of the study, however, if the patient, surgeon, or therapist has concern regarding patient safety, compliance or outcome due to the group assignment, cross-over to the other group will be allowed. The research plan is for approximately a 15% crossover rate based on prior research which planned for 10%, but actually ended up with 30% crossover [37]. The reason for cross-over will be recorded in the electronic health record and reported in the study result.

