### Statistical analysis

#### Sample size

To determine sample size of this parallel design, the study was powered (a-priori) for the primary outcome measure of the American Shoulder and Elbow Surgeon (ASES) scale at baseline, 2 and 6-weeks, 3 and 6 months post replacement. Study assumptions estimate a 12 month ASES score of 79/100 for the PT group (SD = 15.0) and 69/100 for the HT group (SD = 15.0). The 10 point change is considered a clinically meaningful difference in groups [10].

Assuming normal distributions among the 2 independent group ASES measures, and assuming small-to-medium effect based on between-group differences, we constructed a sample size estimation using a Repeated Measures Analysis of Covariance (ANCOVA). Measuring fixed effects, main effects, and interactions, with an expected 80% power, 6 dedicated time intervals (including baseline), two independent groups, 2 covariates, 1 outcome measure, and a standard error of probability of 0.05, we estimate the need for a minimum sample size of 158 for statistical significance (~ 79 per group). To account for the expected potential 24 crossover (15%) subjects, we will increase enrollment to 182 total. Missing values will be adjusted using a chains equation, multiple imputation method in which we will assign predictor, structural and impute variables.

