We will evaluate the primary outcomes with two sets of statistical analyses: One with intention to treat including patients who crossed over and a second adjusted to the cross-overs of the patients. Non-adherence to randomly assigned treatments can often mean that the intention-to-treat analysis underestimates the real benefit of the treatment [48]. We will run a preplanned sensitivity analysis evaluating the descriptive statistics of those who crossed over to those who did not. We will also run an estimated “as treated” longitudinal analysis based on comparisons of those actually treated with PT and HT. We will analyze a repeated measures, linear mixed effect model in which our outcomes will remain the dependent variable and treatment received will be incorporated as a time varying covariate. Adjustments will be made for the time of cross-over with respect to the original enrollment date to approximate the designated follow-up times. Baseline variables that were individually found to predict missing data or treatment received will be included to adjust for possible confounding.

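### The 15% crossover rate is attributed to a study that observed 30%, no reason is given for halving it, and intention-to-treat power is not stated at any crossover rate

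*Protocol article*

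**What the plan says.** Under Eligibility criteria/subjects, the Protocol article plans for "approximately a 15% crossover rate based on prior research which planned for 10%, but actually ended up with 30% crossover". This study is the only source given for the rate. The same section says "cross-over to the other group will be allowed" "if the patient, surgeon, or therapist has concern regarding patient safety, compliance or outcome due to the group assignment", and it names no upper limit. It also encourages patients to stay in their assigned group. It excludes those who will not make a good-faith effort to adhere and those who cannot attend physical therapy.

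The Sample size section reaches a minimum of 158 (about 79 per group) for 80% power, and then: "To account for the expected potential 24 crossover (15%) subjects, we will increase enrollment to 182 total". Its stated assumptions are "Study assumptions estimate a 12 month ASES score of 79/100 for the PT group (SD = 15.0" and "69/100 for the HT group (SD = 15.0", that is, 10 points with SD 15. It also describes the calculation as "assuming small-to-medium effect based on between-group differences", without a number.

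Data analysis primary outcomes plans two sets of analyses: intention-to-treat (ITT) with crossovers kept, and one adjusted for crossover. An as-treated model is added. On the first, the section says: "Non-adherence to randomly assigned treatments can often mean that the intention-to-treat analysis underestimates the real benefit of the treatment".

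**The concern.** A planning rate should follow from its evidence or come with a reason for departing from it. Here the one cited study shows a planned rate exceeded threefold (10% to 30%). The protocol plans at half the observed rate and does not say why. Even the midpoint of 10% and 30% would be 20%.

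The rate matters because crossovers stay in the ITT analysis. A patient who crosses is not lost: that patient carries some of the other arm's effect into the comparison and shrinks the difference. The protocol acknowledges this in words but puts no figure on it, so a reader cannot tell whether 80% power survives at 15%, let alone at 30%.

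The Discussion raises the stakes. It says that the same or better outcomes with home therapy would support surgeon-directed home therapy as the convenient and cost-effective choice. A non-significant ITT result produced by dilution could be read that way.

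**Working it through.** **Inputs.** From Sample size: difference 10, SD 15, alpha 0.05, 80% power, 158, then 182 (91 per arm). From Eligibility criteria/subjects: 1:1 allocation, 15% planned and 30% observed elsewhere. Assumed here: a two-sided, two-sample t test (noncentral t), because sidedness and the repeated-measures settings are not stated.

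**The plan's own figures.**
- 182: 158 × 0.15 = 23.7, rounded to 24, and 158 + 24 = 182. This reproduces. It treats crossovers as losses to be replaced.
- 158: it does not follow from 10 points and SD 15. That needs about 2 × (1.96 + 0.84)² × (15/10)² = 36 per arm (72 in total, normal approximation). At 79 per arm, power is about 99%. An ANCOVA with two covariates gives exactly 158 at f = 0.225 with numerator df 1, or at f = 0.25 with numerator df 2, but the protocol states neither.
- A standardised difference d of about 0.45 (0.4485, or 6.7 points at SD 15) gives 80% at 79 per arm in a two-sample t test. It is used below as a second basis and is an assumption.

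**Dilution.** If shares c_PT and c_HT of the two arms fully take the other arm's effect, the ITT difference is multiplied by 1 − c_PT − c_HT. With 1:1 allocation, the share of all randomised patients is c = (c_PT + c_HT)/2. The multiplier is therefore 1 − 2c, however crossover splits between the arms.
- c = 15%: 10 × 0.70 = 7 points
- c = 30%: 10 × 0.40 = 4 points

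**ITT power under full switching.**

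| Basis | Total N | No crossover | 15% | 30% |
|---|---|---|---|---|
| 10 points, SD 15 | 182 | 99% | 88% | 43% |
| d about 0.45 | 182 | 85% | 56% | 23% |
| 10 points, SD 15 | 200 (Abstract) | 99.7% | 91% | 47% |
| d about 0.45 | 200 (Abstract) | 88% | 60% | 24% |

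**Partial switching.** If crossing patients keep half of their original arm's effect, the multiplier is 1 − c. At 30% it is 0.70, the same as 15% full switching. With 182 patients, power is then 88% on 10 points and SD 15, and 56% on d about 0.45.

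**Does adding 24 patients offset the dilution?** Under 15% full switching, keeping 80% ITT power needs the undiluted total divided by 0.70². On the basis that gives 158, that is 158/0.49 = about 322, far above 182. On 10 points and SD 15, it is 72/0.49 = about 147, which 182 covers. The answer depends on which effect size underlies the 158, and the protocol does not say.

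**The case against.** The other side has real points.

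- **The protocol is open about its evidence.** It reports both 10% and 30% and plans between them. The cited study's population, crossover rules and denominator are not shown, so 30% may not transfer. If it meant 30% of one arm only, that is 15% of all randomised patients, and power on 10 points and SD 15 is 88%. This stands as a caution against treating 30% as the expected rate. It does not supply the missing reason for 15%.
- **Crossover is discouraged.** A reader might infer that nothing in the protocol holds crossover down. The documents contradict that: there are good-faith and attendance exclusions, encouragement to stay in the group, and a bar on extra therapy outside the assigned arm. None of these is linked to 15%, however.
- **ITT is not the only analysis.** A reader might take it as the single primary analysis. The protocol lists two sets without ranking them, plus an as-treated model. Adding 24 patients does suit an analysis without crossovers, but it does not address the ITT dilution.
- **Full switching is extreme.** Therapy runs for about three months, so a late crossover changes little of the exposure, and a repeated-measures model may give different power. This stands, which is why the figures form a range.

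Two stronger readings are tempting and do not hold. The first is that power drops from the stated 80% to 43%. That mixes bases: the inputs giving 43% give 99% without crossover and 88% at 15%. The second is a fixed limit of about 19% crossover, beyond which the trial is underpowered. That figure holds only for 10 points, SD 15, 182 patients and full switching. On d about 0.45, the corresponding limit is about 3%.

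**Conclusion.** The point holds in limited form. The 15% rate is presented as resting on a study that observed twice that rate, with no reason for the reduction. It enters the sample size as a replacement for losses, although one of the two planned primary-outcome analyses keeps crossovers in their randomised arm. The stated 80% is therefore not shown to hold for the ITT analysis at either rate the protocol mentions.

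Under full switching with 182 patients, moving from 15% to 30% crossover takes ITT power from 88% to 43% on 10 points and SD 15, or from 56% to 23% on d about 0.45. If half the original effect is kept, power at 30% is 88% and 56% respectively. These figures assume a two-sided two-sample test and a common SD of 15. The documents do not establish that 30% will occur here or that the trial is underpowered. They show that the planning rate is unsupported and that its consequence is not quantified.

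**What to change.** 1. In Eligibility criteria/subjects and Sample size, either state why a lower rate than 30% is expected here (for example, by linking it to the adherence measures already in place) or stop presenting 15% as supported by the cited study.
2. In Sample size, state which effect size underlies the 158.
3. On that one basis, restate ITT power for the enrolment kept (182, or the Abstract's 200) over 15–30% crossover, showing full and partial switching.
4. In Data analysis primary outcomes, state that a non-significant ITT result will be read from its confidence interval against the 10-point difference, together with the observed crossover rate. It will not be taken as evidence that home therapy is equivalent. Set no fixed crossover threshold.

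The cost is a few sentences and a small table. No extra patients or procedures are needed. The drawback is that the stated power will probably look less favourable.

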### Interventions

#### Rehabilitation management

##### Physical therapy and home therapy groups

Prior to discharge from the hospital or surgical center, all subjects in both study groups (PT or HT) receive the same phase 1 exercise instruction by occupational or physical therapists. Patients in the PT and HT groups follow the rehabilitation guidelines proposed by Boudreau et al. [20] which are detailed in Table 1.

**Table 1 Tab1:** Rehabilitation guidelines for reverse total shoulder arthroplasty

PHASE	PRECAUTIONS AND GUIDELINES	GOALS	EXERCISES	CRITERIA TO ADVANCE TO NEXT PHASE
1 (post-op day 1-2 week)	Sling 24/7 (remove for grooming and HEP-3 5x/day) Avoid hand behind back, and reaching cross body Keep arm anterior frontal plane “always see elbow” No shoulder AROM No submersion in water No weight bearing on shoulder	Protect prosthesis from dislocation Prevent infection Promote distal circulation Proper sling fit PROM: 120 elevation and 30 ER	Pendulum Active elbow, wrist and hand, scapular retraction Passive elevation to 90-120 deg in scapular plane Passive ER to 30 deg inscapular plane	Pain less than 3/10 with PROM Healing incision without signs of infection Clearance by MD after radiograph assessment at 2 week check up
2 (3-6 wks)	Sling only in community Use of operative arm allowed for basic ADLs with elbow beside waist – nothing heavier than a coffee cup. No active reaching from shoulder May submerge in water (eg pool or hot tub) after 4 weeks Continue no shoulder extension, hand behind back, cross body or weight bearing	Passive elevation to 120; ER to 30 Able to fire all heads of deltoid Pain < 3/10	Discontinue elbow, wrist, and hand exs since using arm of ADLs Continue pendulum, scapular retraction, PROM for elevation and ER 120/30 in scapular plane ADD: deltoid isometrics for all heads (avoid extension beyond frontal plane) Reverse pendulum at 90 deg elevation in supine	Passive elevation to 120 and ER to 30 degrees Able to fire all heads of deltoid without pain Able to place and hold arm at 90 deg in supine (balanced position)
3 (6-12 wks)	Discontinue sling Motion recovery without excessive force Advance arm use in ADLs gradually May begin hand behind back gently NO Upper Body Ergometer due to repetitive loading of deltoid on acromion	Optimize PROM Develop AROM to match available PROM Establish dynamic stability of shoulder with deltoid and parascapular strengthening, as well as any rotator cuff remaning	Active forward elevation progression: supine to inclined to vertical, short to long lever arm (bent to straight elbow) Active ER/IR with arm at sideTheraband scapular retraction IR behind back gently	AROM when upright equals PROM in supine No pain Need higher level demand than ADL functions (eg sport or work)
4 (12+ wks)	Avoid heavy lifting and overhead sport Avoid heavy pushing May lift light weights for deltoid but not to exceed 3 lbs NO Upper Body Ergometer	Functional demands for work and/or sport achieved Gradual increase in deltoid and parascapular muscle strength Painfree	Weights for deltoid up to 3 lbs max, using short lever arm (bent elbow) for middle deltoid raise Theraband progression for scapular muscles, including serratus anterior punches Gentle end range stretching in all planes as part of a daily lifelong routine	NA

##### Physical therapy intervention group

Subjects in the PT group will begin out-patient clinic-based rehabilitation 4–5 days after discharge from the hospital and continue in therapy approximately once a week for three months. Physical therapists will employ a pragmatic approach within the rehabilitation guidelines summarized in Table 1. Physical therapists will determine the optimal exercises for each patient within the specified guidelines for each phase of recovery. The exercises may vary amongst subjects considering patient specific variables such as exercise tolerance and pain response, ease of progressing to next level of challenge, ability to follow directions and perform exercises correctly, and individual goals for rehabilitation. The number of physical therapy visits may vary amongst patients in this group depending on response to therapy. For example, patients with low demand goals for rehabilitation and/or those who tolerate therapy well and advance easily may need less PT visits than patients with high demand goals and/or those who don’t tolerate therapy well and progress more slowly.

##### Home therapy group

Patients continue to perform the exercises they learned in the hospital prior to discharge until they follow-up with the surgeon per the standard of care approximately 2 weeks after surgery. Rehabilitation exercises and activity guidelines will be advanced for the HT group by the treating surgeon using pre-printed exercise handouts which follow the rehabilitation guidelines in Table 1. The handouts will not vary amongst subjects for consideration of patient specific variables. All subjects will receive the same exercise progression at the 2 week, 6 week, and 3 month appointment.

Additional physical therapy following the RTSA procedure (not in the PT or HT group) will not be allowed. Other physical care such as chiropractic or massage intervention for conditions not related to the RTSA procedure will be allowed upon approval by the treating surgeon.

### Data collection

#### Descriptive information

Patient age at time of surgery, sex, height, weight, hand dominance, laterality of surgery, reason for RTSA (cuff tear arthropathy, primary osteoarthritis, or massive rotator cuff tear with pseudoparalysis), history of prior ipsilateral shoulder surgery (e.g. rotator cuff repair), history of prior ipsilateral shoulder fracture, and history of prior ipsilateral shoulder dislocation, and the type of RTSA prosthesis employed in procedure will be obtained from the medical record. Final data will be kept confidentially at the lead institution.

#### Primary outcomes

The American Shoulder and Elbow Surgeons (ASES) questionnaire is a standardized method of evaluating shoulder pain and function. This instrument is a 100-point scale which assesses pain (50 points) and activities of daily living (50 points), and has demonstrated good reliability/validity following shoulder arthroplasty [38]. The ASES score clinically important change following shoulder arthroplasty is 9 to 10 points [11, 39].

Pain level is monitored using the 0–11 numeric pain rating scale (0 = no pain; 10 = worst pain imaginable) at present, as well as the best and worst rating over the 2 week interval preceding assessment.

The Single Assessment Numeric Evaluation (SANE) score asks a patient the question: “How would you rate your affected joint/region of interest today as a percentage of normal (0% to 100% scale) with 100% being normal?” and has been validated for patients having shoulder arthroplasty [40].

The Patient-Reported Outcomes Measurement Information System (PROMIS-29) version 2 .0 profile assesses pain intensity (0 to 10) as well as seven health domains including physical function, fatigue, pain interference, depressive symptoms, anxiety, social interactions, and sleep disturbance with 4 items per domain. The physical health factor (physical function, pain intensity and interference, and social interactions) and mental health factor (anxiety and depressive symptoms) have been established as valid and reliable [41]. The PROMIS has been determined to be a responsive instrument following RTSA [42].

##### Range of motion

Passive and active scaption, external rotation with the arm at the side (ER0), external rotation at 90 degrees of abduction in the scapular plane (ER90), and active internal rotation (IR) range of motion are measured pre-operatively and at 6 weeks, 3 months, 6 months, 1 and 2 years post-operatively. Active range of motion is measured at the end of the range of motion self-selected by the subject with the instruction to move as far as possible without pain. Passive range of motion is provided by the measurer with the instruction “Please allow me to move your arm as far as possible without increasing pain.”

Standardization of the method of measuring ROM was deemed necessary due to the multi-center nature of this trial employing several research assistants to obtain measures. A custom device for guiding scaption (elevation 30 degrees anterior the frontal plane), and a custom device for stabilizing the arm for ER measures were constructed (Figs. 1, 2 and 3). A validated smart-phone inclinometer application (Clinometer, plaincode, www.plaincode.com) is used to measure scaption and ER(90) [43]. A goniometer is used to measure ER(0), and the Constant-Murley method of scoring functional IR is utilized [44].

**Fig. 1 Fig1:**
[figure not shown]
**A**. Start position for measuring scaption. **B**. End position for measuring scaption

**Fig. 2 Fig2:**
[figure not shown]
**A**. Set up for measuring external rotation in neutral position with the arm at the side. **B**. Measuring scaption with subject’s arm placed on top of the goniometer

**Fig. 3 Fig3:**
[figure not shown]
**A**. Set up for measuring external rotation at 90 degrees of abduction. **B**. Patient, and **C** Clinometer positioning for measuring active and passive external rotation at 90 degrees of abduction

Scaption is measured by having the subject elevate the arm along a plastic pipe anchored to a base placed 30 degrees anterior the frontal plane (Fig. 1a). The clinometer application is zeroed with the arm at the side prior to scaption and read at the end of the active or passive motion (Fig. 1b). ER (0) is measured by stabilizing one arm of a plastic goniometer to a forward facing plastic pipe placed beside the subject, with the axis of the goniometer under the subjects’ elbow (Fig. 2a). The mobile arm of the goniometer is aligned under the ulnar side of the forearm at the end of the ER (0) motion (Fig. 2b). ER (90) is measured with the upper arm stabilized to a plastic pipe at shoulder height oriented in the scapular plane (assumed at 30 degrees anterior the frontal plane), and the participant rotates the forearm up from a second plastic pipe which is forward facing (Fig. 3a). The Clinometer is zeroed at the horizontal, and read at end range of ER (90) (Fig. 3b and c). Internal rotation is only measured actively, not passively, by observing the highest anatomic landmark achieved using the Constant-Murley scoring method [44].

